# Introduction

Chronic Heart Failure (CHF) is a cardiovascular condition characterized by progressively debilitating symptoms and frequent life-threatening exacerbations (1, 2), affecting 26 million individuals globally, along with their families (2) . Patients with CHF are confronted with numerous physical burdens, arduous medical treatments, and profound lifestyle adjustments (3-5) . They also experience uncertainty in illness, fear of sudden death, anxiety, depression, and non-adherence to recommended self-care activities for CHF. These factors are often intertwined and linked to compromised health-related quality of life (HRQOL) for CHF patients (6-10). Family caregivers (FCs) are essential in providing emotional and practical support to CHF patients to improve health outcomes (11, 12). However, after the diagnosis of CHF, the majority of FCs (94%) experience occupational, physical, psychological, and social burdens (13), with nearly 86.7% of FCs indicating high levels of caregiving burden (14). A considerable proportion of FCs report depressive symptoms (23% to 47%) (15) and anxiety (50%) (16). The psychological states of both caregivers and patients are linked to the HRQOL of FCs (17-19). During the process of managing CHF, family conflicts, relationship issues, and communication problems have been reported as consequences of psychological distress in families living with CHF(20, 21). FCs’ HRQOL is as impaired as that of CHF patients (17).

Clinical guidelines for managing CHF emphasize the importance of incorporating FCs in the CHF care process (22, 23). Research has indicated that dyadic interventions, which involve both patients and FCs, are promising in reducing hospital readmission rates and improving the health-related quality of life (HRQOL) for patients with chronic illness, and better mental health outcomes for FCs by facilitating disease self-management (24, 25). However, non-pharmacological aspects when combined with the efforts of FCs in the context of CHF home care have been understudied (26). In a recent systematic review (26), three experimental studies provided non-pharmacological support to optimize HRQOL and related outcomes for CHF patients and their FCs (27-29). The studies mainly employed strategies such as providing education and psychological support to patients and caregivers after discharge, but the impact on HRQOL and other outcomes remained inconclusive. Moreover, the psychological component employed including cognitive-behavioral therapy (CBT), and motivation enhancement, may not be sufficient to promote CHF self-management (30), and may even result in patients avoiding recommended self-management behaviors (31), potentially leading to poor health outcomes.

Acceptance and commitment therapy (ACT) is a therapy that focuses on the context in which thoughts and emotions occur, with the goal of changing the functions of problematic behavior rather than altering cognitive content (32). By fostering acceptance of private experiences and decreasing fusion with negative thoughts, ACT can promote HRQOL by allowing individuals to behave in line with their values and lead a meaningful life (32). However, empirical research on the use of ACT to improve HRQOL for CHF patients and their FCs is scarce. While recent systematic reviews have shown promising effects of ACT on the HRQOL of patients with chronic illness (33) and FCs (34), most studies have been conducted at the individual level with less attention paid to the circumstances of context. Two pilot studies conducted among patients with advanced cancer have shown early support for the use of a remote ACT intervention for patient-FC dyads, but with no statistically significant differences found in HRQOL, usage of health services, and caregiver distress when compared to the usual care (35, 36). Methodological shortcomings, including the exclusion of relational measures, the use of a telephone-based modality, and small sample sizes, may limit the validity of the studies. Previous studies indicated that establishing a group context and using commonly accessible videoconferencing platforms (37, 38)may improve the effects of an ACT intervention.

Given the shortcomings and strengths of these interventions and considering the availability of patients and their FCs and the potential positive effects of group-based interventions, what might be needed is an online, videoconferencing, group-based intervention using ACT for patients and FCs. This protocol of study aims to bridge the gap by testing the effectiveness of group-based dyad-orientated ACT for patients and their family caregivers.

**2 Methods**

**Objectives**

This study is proposed with the objective of evaluating the effectiveness of a dyad ACT-based intervention delivered via smartphone for CHF patients and their FCs compared with CHF education only at a 3-month follow-up on: (1) Patient and FC outcomes: HRQOL (primary outcome), perceived health status, anxiety, depressive symptoms; perceived quality of the relationship, psychological flexibility, self-compassion, and perspective-taking; (2) Patient-only outcomes: Hospital service utilization; CHF self-care behavior; and (3) Caregiver-only outcome: Caregiving burden.

**Study design**

The proposed study is a two-armed, parallel-group, equivalence randomized controlled trial (RCT). Dyads of CHF patients and their FCs will be randomized at a 1:1 ratio to either the intervention group, which will receive an ACT-based intervention, or the control group, which will receive only CHF education.

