## A prior power analysis was performed to estimate the sample size needed in this study using G*Power. Previous studies in CHF have shown that mean differences in HRQOL between patients who received a psychosocial intervention and the usual care ranged from 0.11 to 0.68 (42). For ACT interventions targeting HRQOL, a recent review meta-analysis reported a mean effect of 0.48 for the clinical and non-clinical population, ranging from 0.37 to 1.55 when those who received the ACT intervention were compared to the active control, not including CBT (43). Thus, an estimated effect size of 0.50 was adopted across the above reviews. Targeting that effect size at a power of 0.8 with a prior power calculation, a minimal sample size of 128 is required to detect the difference between the ACT group and CE groups. Considering a weighted dropout rate of 16% for those participating in an ACT intervention indicated in a recent meta-analysis (44), and given group-setting and patient-caregiver dyadic participant requirements for the interventions, the total sample size was increased to 160 patient-FC dyads, accounting for an anticipated dropout rate of 20%.

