# Statistical analysis

All quantitative data collected from the participants will be numerical coded, and analyzed utilizing IBM SPSS 27. Baseline sociodemographic and clinical data will be used using medians, proportions, and counts for categorical data; while means, standard deviations (SDs), skewness, and kurtosis will be used for continuous variables for participants in two groups. Differences in the participants’ characteristics at baseline will be explored using an independent T-test or Mann-Whitney U test for continuous variables, and Chi-squared or Fisher’s Exact test for categorical variables. The primary outcome and secondary outcomes will be summarized using means with SDs for the ACT group and CE groups. Randomized testing at baseline between the study groups will be performed to identify potential covariates. The differences in these outcomes between the ACT group and the CE groups over time will be analyzed using generalized estimating equations (GEE) which account for missing data at random. If any covariance is detected in the baseline comparison, it will be adjusted in the analysis of the effects of the intervention. Subgroup analysis will be adopted for specific factors (e.g., intervention completion and non-completion). The level of statistical significance is predetermined at p<0.05 (two-tailed). The intention to treat principle will be applied by comparing the ACT group with CE groups as randomized despite adherence to the intervention. Cohen’s d will be calculated to estimate effect sizes of between-group comparisons.

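### The Study design section labels the trial an equivalence RCT, but its sample size and test are those of a superiority trial and the protocol states no equivalence margin

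*Protocol*

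**What the plan says.** The framework is named once, in the Study design section: "The proposed study is a two-armed, parallel-group, equivalence randomized controlled trial (RCT". In the same section dyads "will be randomized at a 1:1 ratio".

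Other parts of the protocol are written around finding a difference:

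- **Aim.** The Introduction speaks of "testing the effectiveness of group-based dyad-orientated ACT for patients and their family caregivers". The Objectives section speaks of "evaluating the effectiveness of a dyad ACT-based intervention delivered via smartphone for CHF patients and their FCs compared with CHF education only".
- **Sample size calculation.** "an estimated effect size of 0.50 was adopted across the above reviews". The text continues "Targeting that effect size at a power of 0.8 with a prior power calculation" and concludes that "a minimal sample size of 128 is required to detect the difference between the ACT group and CE groups". The total is then raised to 160 dyads for 20% dropout.
- **Statistical analysis.** Between-group differences over time are analysed by GEE. "The level of statistical significance is predetermined at p<0.05 (two-tailed".

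The protocol gives no equivalence margin, no confidence-interval rule and no pair of one-sided tests. It also gives no reason to expect or seek similar outcomes in the two arms.

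**The concern.** Equivalence and superiority trials have opposite null hypotheses. In an equivalence trial the null is that the arms differ by at least a pre-set margin, and the trial succeeds when the whole confidence interval lies inside that margin. In a superiority trial the null is no difference, and failing to reject it is inconclusive. A plan that carries the first name and the second set of calculations leaves unclear what its result will mean.

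The ambiguity bites when the result is not significant. Under the equivalence label, a p-value above 0.05 invites the reading that ACT and CHF education do equally well. Under the test actually planned, the same p-value says only that no difference was shown. Such a result is a realistic prospect. The comparator is an active programme with the same number and length of sessions, and the Introduction reports two earlier dyadic ACT pilots with no significant difference in HRQOL against usual care.

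**Working it through.** **Inputs.** Effect size 0.50, power 0.80, total 128, dropout 20% and 160 dyads come from the sample size section. Two-tailed alpha 0.05 comes from Statistical analysis, and 1:1 allocation from Study design. Equivalence margins are my assumptions, in SD units, because the protocol gives none.

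**Step 1: reproduce the stated sample size.** For a two-sided comparison of two means, the normal approximation is

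n per arm = 2 × (1.960 + 0.842)² / 0.50² = 62.8, so 63 (126 in total).

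The exact two-sample t-test, with noncentrality 0.50 × √(n/2), gives power 0.795 at 63 per arm and 0.801 at 64. So 64 per arm, **128 in total**, as stated. Dropout: 128 / (1 − 0.20) = **160**, as stated. A one-sided t-test would give 51 per arm (102) and does not match. The trial was sized for a two-sided test of difference.

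**Step 2: precision at 64 evaluable per arm.** SE = √(2/64) = 0.177 SD.

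- 90% CI half-width: 1.645 × 0.177 = 0.29 SD
- 95% CI half-width: 1.960 × 0.177 = 0.35 SD

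**Step 3: power to show equivalence.** With two one-sided 5% tests and a true difference of zero, power = 2Φ(margin/SE − 1.645) − 1, set to zero when negative. The total needed for 80% power is twice n per arm, where n per arm = 2 × ((1.645 + 1.282)/margin)², rounded up.

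| Assumed margin (SD) | margin/SE − 1.645 | Power at 64 per arm | Evaluable total for 80% power | With 20% dropout |
|---|---|---|---|---|
| 0.2 | −0.51 | about 0% | 858 | 1,073 |
| 0.3 | 0.05 | 4% | 382 | 478 |
| 0.4 | 0.62 | 46% | 216 | 270 |
| 0.5 | 1.18 | 76% | 138 | 173 |

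If nobody dropped out (80 per arm), the powers would be about 0%, 20%, 62% and 87%.

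**Step 4: how often the planned test misses a real difference.** With 64 per arm, the two-sided t-test is non-significant about 80% of the time if the true effect is 0.2 SD, 61% if it is 0.3 and 39% if it is 0.4. A non-significant p-value is therefore common when the arms truly differ.

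**The case against.** The best reply is that this is one misplaced word. An analyst who follows the Statistical analysis section will run a two-tailed test of difference and report Cohen's d, whatever the design sentence says. Sample size, randomisation, outcomes and alpha would all stay as they are after correction. The word superiority appears nowhere in the protocol, so that intent is inferred. A separate SAP may exist, and it is not at hand.

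Much of this stands. The intent is an inference, though the aim, the sample size and the test all agree on it, so the sponsor should confirm it. An unseen SAP does not remove the point, because the conflict lies between the protocol's own statements and a later document could not make both true.

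Three stronger readings are tempting, and the protocol does not support them:

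- *The label contradicts every part of the plan.* It does not. Intention to treat, GEE and 1:1 allocation fit either framework. The clear conflicts are the basis of the sample size and the test of difference.
- *The investigators plan to report a null result as equivalence.* Nothing says so. The label creates that risk, but it is not a stated plan.
- *With a 0.5 SD margin, the trial would call equivalent the very effect it is sized to detect.* A true difference equal to the margin lies on the boundary of the null hypothesis, so equivalence would be declared only about 5% of the time. The fair statement is that such a margin would treat differences somewhat below the planning effect as unimportant.

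**Conclusion.** The point holds as an internal contradiction. The design is called equivalence, while the sample size and the test are for superiority, the effectiveness aim points the same way, and no margin or equivalence rule is stated. The figures of 128 and 160 are correct for the trial that was actually sized.

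The consequence is for interpretation. For assumed margins up to 0.3 SD the planned trial would have almost no chance of showing equivalence, and even at 0.5 SD its power falls short of 80%. A non-significant result from the planned test could not support an equivalence claim.

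The power figures rest on assumed margins, 64 evaluable per arm, a true difference of zero, one-sided 5% tests and an unadjusted comparison of two means at one time point. Other assumptions would move them, but the contradiction does not depend on them. It is more than clerical, because it governs what the trial may conclude.

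**What to change.** Ask the sponsor to confirm that superiority is intended. If so:

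1. In Study design, replace equivalence with superiority and state the null hypothesis of no difference, tested at the two-sided 5% level already set in Statistical analysis.
2. In Statistical analysis, add that a non-significant result will be reported with its 95% CI and will not be read as equivalence.

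This costs one word and a sentence or two, plus alignment of any registry or ethics text that repeats the label. The sample size stays at 160 dyads. The change should be made before results by arm are known.

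If equivalence really is intended, a wording change will not do. The protocol must then set and justify a margin, state the confidence-interval decision rule and recalculate the sample size. On the assumptions above that means from 173 dyads (margin 0.5 SD) to 1,073 dyads (margin 0.2 SD) after 20% dropout.

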**Study setting**

## The participants will be recruited from the Department of Cardiology at Taihe Hospital in Shiyan City, China. The hospital is the largest public hospital in Shiyan city, which as a total population is 3,209,004, according to the 2020 census (39). The Department of Cardiology is responsible for the prevention, treatment, and rehabilitation of residents with cardiovascular disease, including CHF.

## Annually, about 3,600 patients are hospitalized with a diagnosis of CHF. After CHF patients are discharged from the hospital, they will be expected to visit the heart failure clinic to review their health condition every one to three months. They will also receive the usual care, which is in line with national and local clinical CHF guidelines in mainland China (23). The usual care includes follow-up telephone calls to provide educational support based on the inquiries of patients and to remind patients of the necessity of undergoing a medical check-up conducted by a physician one week after discharge and by a clinical nurse one month after discharge.

# Eligibility

## Participants of the present study involve both patients with CHF and their corresponding primary FCs. CHF patients will be eligible if they are 18 years of age or older, have been clinically diagnosed with CHF (40) as indicated in their electronic medical records, and with a New York Heart Association (NYHA) Classification of I to III as confirmed by a physician in this study, have been hospitalized in the past one year. CHF patients will be asked to nominate their primary FC, who would be the one with the highest average number of contact hours among their family members, to join the program. FCs should have aided patients with care needs for a minimum of 14 hours per week consistently for at least three months. FCs should be 18 years of age or older, and they can be patients’ spouse, parent, or adult child, but not a paid caregiver or other relative. In addition, at least one member of the patient-caregiver dyad will be required to have a smartphone installed with the WeChat app and a data plan. Both members should understand and communicate in Chinese, as well as be able to access Tencent VooV Meeting via smartphone to attend the sessions.

## Dyads will be excluded from the program if either member has a cognitive impairment screened with a score of 0-2 on the Mini-Cog scale (41) and a documented medical history of psychiatric illness, dementia, or a life-threatening illness, such as severe pulmonary disease or end-stage renal failure. The dyads of patients who live in nursing homes will also be excluded.

## Patients and their FCs will be required to participate in the group sessions on a dyad basis. During the intervention period, if either member has been hospitalized, sessions will be suspended during the period of hospitalization and will resume after she/he is discharged to go home.

# Sample size calculation

## A prior power analysis was performed to estimate the sample size needed in this study using G*Power. Previous studies in CHF have shown that mean differences in HRQOL between patients who received a psychosocial intervention and the usual care ranged from 0.11 to 0.68 (42). For ACT interventions targeting HRQOL, a recent review meta-analysis reported a mean effect of 0.48 for the clinical and non-clinical population, ranging from 0.37 to 1.55 when those who received the ACT intervention were compared to the active control, not including CBT (43). Thus, an estimated effect size of 0.50 was adopted across the above reviews. Targeting that effect size at a power of 0.8 with a prior power calculation, a minimal sample size of 128 is required to detect the difference between the ACT group and CE groups. Considering a weighted dropout rate of 16% for those participating in an ACT intervention indicated in a recent meta-analysis (44), and given group-setting and patient-caregiver dyadic participant requirements for the interventions, the total sample size was increased to 160 patient-FC dyads, accounting for an anticipated dropout rate of 20%.

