# Interventions

Participating dyads will be allocated to either the intervention group or the control group. All of them will receive four identical weekly sessions via the Tencent VooV meeting over four consecutive weeks in addition to the usual care provided by the department of cardiology. Each session will include four to eight dyads and last approximately two hours, and will be led by a registered nurse(s) with technical support from two research assistants throughout the sessions. Participants will receive relevant materials and handouts prior to the first session, and they will be instructed to retain these materials and handouts throughout the duration of the study and beyond. The online sessions will be scheduled on weekday evenings and weekend afternoons to accommodate typical family events and work schedules. During the period of the interventions, WeChat voice calls or text message reminders will be sent to the dyads before each session to improve participant retention and support engagement in the program.

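### The 0.8 power assumes no correlation among dyads treated in the same session group: 160 is exactly the dropout allowance, and the GEE names no session-group level

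*Protocol*

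**What the plan says.** - **Allocation.** Under Study design: "Dyads of CHF patients and their FCs will be randomized at a 1:1 ratio". Randomization and blinding confirms that the dyad, not the session group, is the unit of randomisation.
- **Delivery.** Under Interventions, for both arms: "Each session will include four to eight dyads and last approximately two hours". There are four weekly sessions. From session 2 on, each starts from or includes a review of what came before, which suggests stable groups, although fixed membership is not stated.
- **Sample size.** "an estimated effect size of 0.50 was adopted across the above reviews". Then: "Targeting that effect size at a power of 0.8 with a prior power calculation, a minimal sample size of 128 is required". The increase to 160 mentions the group setting ("given group-setting and patient-caregiver dyadic participant requirements for the interventions, the total sample size was increased to 160 patient-FC dyads") and is described as "accounting for an anticipated dropout rate of 20"%. No ICC or design effect appears.
- **Analysis.** Under Statistical analysis, differences between arms over time "will be analyzed using generalized estimating equations (GEE) which account for missing data at random". The clustering unit, the working correlation and the variance estimator are not named.

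**The concern.** Dyads who share a group for four weeks may end up with more similar outcomes than dyads in different groups. The Introduction itself argues that a group context may strengthen ACT, so some within-group correlation is foreseeable. Individual randomisation does not remove it, because the correlation arises after allocation through shared treatment.

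Two things are at stake. First, with positive correlation, 128 evaluable dyads carry less information than 128 independent ones, so power falls below the stated figure. An analysis plan cannot restore information that a fixed total of 160 does not supply. Second, a GEE clustered only on the participant or the dyad would still treat dyads from one session group as independent. Its standard errors would then be too small, and the error would favour declaring an effect on the primary outcomes.

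**Working it through.** **Inputs from the Protocol.** Standardised effect 0.50; power 0.8; 128 evaluable (64 per arm at 1:1); dropout 20%; groups of 4 to 8 dyads. The sample size paragraph names no alpha, so it is taken from Statistical analysis: "The level of statistical significance is predetermined at p<0.05 (two-tailed)".

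**Assumptions, not in the Protocol.** ICC of 0.01, 0.05 or 0.10; m = 5 evaluable dyads per group (the mid-range group of 6 less 20% is 4.8); total variance equal in both arms.

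**Step 1: reproduce the plan.** A two-sample t-test (noncentral t) with d = 0.50, two-sided alpha 0.05 and 64 per arm has power 0.801, so 128 is reproduced. Dropout: 128/(1 − 0.20) = 160 exactly. The whole increase is used by dropout.

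**Step 2: same ICC in both arms.** Design effect DE = 1 + (m − 1) × ICC. Effective n = 128/DE. Power comes from the noncentral t with 64/DE per arm. Type I error of a test that ignores the group = 2 × [1 − Φ(1.96/√DE)].

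| ICC | DE | Effective n | Power | Type I error if group ignored |
|---|---|---|---|---|
| 0.01 | 1 + 4 × 0.01 = 1.04 | 123 | 0.79 | 5.5% |
| 0.05 | 1 + 4 × 0.05 = 1.20 | 107 | 0.73 | 7.4% |
| 0.10 | 1 + 4 × 0.10 = 1.40 | 91 | 0.66 | 9.8% |

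With degrees of freedom based on the number of groups (128/5 − 2, about 24), power is 0.76, 0.70 and 0.63.

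**Step 3: clustering in the ACT arm only.** The variance of the difference is inflated by (DE + 1)/2.

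| ICC (ACT only) | Inflation | Power | Type I error if group ignored |
|---|---|---|---|
| 0.05 | (1.20 + 1)/2 = 1.10 | 0.76 | 6.2% |
| 0.10 | (1.40 + 1)/2 = 1.20 | 0.73 | 7.4% |

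**Step 4: largest groups.** A group of 8 less 20% leaves 6.4. At ICC 0.05 in both arms, DE = 1 + 5.4 × 0.05 = 1.27 and power is 0.70.

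**Step 5: slack if dropout is lower.** At the literature rate of 16%, 160 × 0.84 = 134.4 dyads are evaluable, and 134.4/128 = 1.05. At m = 5 that absorbs an ICC of about 0.05/4 = 0.0125.

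**Step 6: number of groups.** 160/8 = 20 to 160/4 = 40 groups in all.

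**The case against.** - **The ICC is unknown and could be small.** This stands. At 0.01 the power loss is about 1 to 3 points. The same two nurses deliver ACT and one nurse delivers the education arm, so facilitator differences do not vary between groups within an arm. Group composition and interaction remain as sources.
- **One ICC for both arms may be too harsh.** This stands. The education sessions are largely didactic, hence the ACT-only figures.
- **The Protocol does not say that the analysis treats dyads as independent.** This stands. A reader might infer that the standard errors are too small and that type I error is inflated. The text does not support that as fact: the GEE clustering unit is unstated, and an analysis plan that is not shown could define it. The inflation holds only if the group is omitted and its ICC is positive.
- **The group setting may be mentioned only as a reason to expect more than 16% dropout.** That is a fair reading of the sentence. It leaves the result unchanged, because under either reading no clustering allowance exists.
- **Repeated measures may recover power.** Partly so. The 128 is a single-time calculation, whereas a baseline and two follow-ups are collected. With an assumed baseline correlation of 0.5 (variance × 0.75), power at DE 1.20 is about 0.84; with 0.3 (variance × 0.91), about 0.77. Net power is therefore uncertain, but baseline adjustment does not correct the type I error.

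**Conclusion.** The point holds in conditional form and is a should-fix. What the Protocol establishes is that both arms are group-delivered, that 128 assumes independent dyads, that 160 contains only the dropout allowance, and that no session-group level is named in the analysis. At the planned dropout, and on the Protocol's own method, any positive session-group ICC takes power below 0.8.

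The size depends on the assumed ICC. The loss is minor at 0.01 and material from about 0.05, where power is about 0.73 with clustering in both arms or 0.76 with clustering in the ACT arm alone. A reader might conclude outright that the trial is underpowered; without an ICC, and with possible gains from baseline adjustment, the document does not settle that.

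**What to change.** 1. **Sample size calculation.** Restate the power of 160 dyads with a declared ICC, group size and design effect, for example about 0.73 at ICC 0.05 in both arms with 5 evaluable dyads per group. Alternatively, justify an ICC near zero. Say plainly that the 20% is for dropout only.
2. **Data and analysis.** Record the session-group ID from the first session, since it may be hard to reconstruct later. Include it in the primary analysis in one of two ways:
   - a mixed model with repeated measures and a random intercept for session group, its variance allowed to differ by arm, with Satterthwaite or Kenward-Roger degrees of freedom; or
   - GEE clustered on session group with a small-sample variance correction, since there will be only about 20 to 40 groups.

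**Cost.** A change of wording and one database variable. The stated power becomes slightly less favourable and the intervals slightly wider. No extra patients are needed.
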